## Methods

2

### Study design and participants

2.1

The ENERGYCO study is a cluster randomized controlled trial to be conducted in high schools from three Spanish cities (Granada, Jaén, and Almería), where the schools will be the units of randomization, and individuals within the schools will be the units of analysis (participants). This project will consist of two main phases: Phase I will present a cross-sectional design which will take place before starting the Phase II. A cross-sectional approach will be adopted due to its suitability for capturing a snapshot of key variables of interest at a specific point in time, aligning with the objectives of this phase (i.e., comparing PAEE associated with different modes of commuting to school and developing predictive equations for measuring PAEE in Phase II). In contrast, for Phase II a cluster parallel-arm design will be employed to allocate interventions effectively to larger groups while accounting for potential intra-cluster variability, enhancing the external validity and generalizability of the results. The ENERGYCO study has been approved by the Review Committee for Research Involving Human Subjects at the University of Granada (Reference: 2496/CEIH/2021) and registered with a ClinicalTrials.gov ID: NCT06414668. In addition, the present study protocol has been written in accordance with the Standard Protocol Items: Recommendations for Interventional Trials (SPIRIT) statement (See Supplementary material 1).

### Study population

2.2

In the Phase I of the ENERGYCO study, a convenience sample of 50 students (12–16 years old) will be recruited to assess the PAEE of different modes of commuting to school (i.e., walking, cycling, and motorized-vehicle). For Phase II, the ENERGYCO study will recruit a random sample of students (*n* = 300) from the three Spanish cities (i.e., Granada, Almería, and Jaén). The intervention aims to assess the effects of a school-based cycling intervention in the RMR and PAEE related to cycling to school, as well as its impact on others physiological, physical, emotional, and psychosocial outcomes in Spanish adolescents. The randomization process is presented in Figure 1.

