
**Table 1 tab1:** Schools’ inclusion and exclusion criteria.

Inclusion criteria	Exclusion criteria
The school has a specific space for parking bicycles and allows their parking	The school does not have specific infrastructure to park or store bicycles
The school has at least two classes per grade	The school offers bus transportation to the adolescents
At least eight students from the school will agree to participate in the study	The school is already participating in other interventions focused on promoting healthy behaviors
Schools from urban areas	The school has implemented an intervention to encourage commuting to school within the last year
	Schools from rural areas

**Table 2 tab2:** Participants’ inclusion and exclusion criteria.

Inclusion criteria	Exclusion criteria
Adolescents’ females and males aged from 12 to 17 years old (both ages included)	Adolescents younger than 12 years or older than 17 years
Healthy participants who can ride a bicycle safely and without difficulty.	Participants with any injury or medical condition that prevents safe participation in cycling to and from school
Be able to cycle to and from school at least 3 days per week during eight consecutive weeks (Intervention group)	Insufficient ability to ride a bicycle or inability to cycle to and from school at least 3 days a week (Intervention group)
Not to cycle to and from school more than 3 days a week during the last year	Participants who have cycled to and from school more than 3 days a week during the past year
To present a valid signed consent from their parents or legal guardians	Participants without a valid, signed parental or guardian consent form
To present valid data at baseline and follow-up from all the outcomes assessed	Participants who do not provide valid data for all assessed outcomes at baseline and follow-up

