#### Study assessment protocol

2.6.1

In Phase I, participants will perform three different simulations (i.e., commute by motorized-vehicle, walking, and cycling [see Figure 2]): (1) a simulation of driving to school will be performed by motorized-vehicle. After all the calibration process of the Cosmed K5 (both, flow and gas analyzers will be calibrated before every gas exchange measurement), a face-mask attached to the K5 will be place and gas exchange will be check during a two-minute period before the measurement start. After the check phase, gas exchange recording start during a five-minute period, while participants remain seated. Then, the participants will simulate commute in a motorized-vehicle by remaining seated in a chair for another 15-minute period, having previously walked for 2 mins simulating that participants are moving toward the motorized-vehicle from home. After this first simulation, there will be a five-minute period of cooling down. The total time of this first test will be 27 min. (2) A simulation walking to school will be conducted in a closed circuit defined by the research staff. The same procedures mentioned before will be followed. Then, the participant will walk for 15 min (the participant will determine the speed and intensity of walking) and finish with a five-minute cool down; (3) Participants will simulate a cycling route. They will wait for five-minute after walking and they will start cycling during 15-minute period along the designated route. The simulation will finish with a five-minute cool down period. The total time used in the walking and cycling simulations will be 45 min. These times were chosen because an average walking speed of 4.4–4.6 km/h would not exceed the distance Spanish adolescents are willing to walk to their educational center (1,350 m) (52). While no study in Spanish adolescents indicates the distance, they are willing to cycle to school, we estimated a distance of 4,200 m, the threshold distance used for Australian adolescents (53), with which a speed of approximately 15 km/h would not exceed 15 min. Detailed visual information on the evaluation and calibration process of the Cosmed K5 (Cosmed, Rome, Italy) can be found at the following link.^1^ In order that one active mode of commuting (e.g., walking) does not affect the post exercise oxygen consumption, thus PAEE, of the subsequent active mode of commuting (e.g., cycling), participants will alternate randomly by first performing the simulation of walking or cycling. In addition, the alternation of starting on the bike and walking will be counterbalanced by having the same number of participants starting on the bike or walking. Finally, all data will be downloaded using PC OMNIA.9 software v3.30.79 (Cosmed, Rome, Italy).

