##### Energy expenditure related to active commuting to school

2.7.1.2

PAEE related to different modes of commuting to school (i.e., walking, cycling, passive modes) will be measured using the Cosmed K5 portable metabolic system in Phase I. The Cosmed K5 has previously shown a good level of agreement compared to stationary metabolic carts at low cycling intensity (5.8% difference in VO_2_). At moderate intensities, it slightly underestimated VO_2_, VCO_2_, and energy expenditure (~6.6–6.9%). Additionally, during walking tests, the Cosmed K5 demonstrated high reproducibility, with a coefficient of variation of 4.5% for energy expenditure per kilometer and a concordance coefficient of 0.91. VO_2_ measurements were consistent, with low variability in the fraction of expired oxygen (coefficient of variation of 0.9%) (56). The Cosmed K5 is worn on the back with a harness and measures oxygen consumption (VO_2_) and carbon dioxide production (VCO_2_) in breath-by-breath mode. Before each assessment, the device will be calibrated using a reference gas mixture of 15.92% O_2_ and 5.03% CO_2_. Delay calibration for the breath-by-breath mode will also be performed (57). During the test, participants will breathe normally while commuting, and the Cosmed K5 will record data continuously. Data will be analyzed as the mean VO_2_ and VCO_2_ (ml/min) during each commuting mode. In Phase II, PAEE related to cycling will be estimated using predictive equations developed in Phase I. These equations will incorporate variables such as distance, speed, and heart rate, and will be cross-validated against PAEE measurements obtained with the Cosmed K5 to ensure accuracy. Therefore, data will be analyzed as the mean VO_2_ and VCO_2_ (ml/min) during each cycling trip to and from school, aggregated by participant during the intervention period.

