##### School characteristics

2.7.2.20

School characteristics will be assessed using various measures. School size will be determined based on student enrollment, reflecting the total number of students enrolled during the study period. School socioeconomic status (SES) will be established using data from previous studies (91). Additionally, the socioeconomic status of the school neighborhoods will be objectively analyzed and classified as high or low using GIS. Moreover, the length of the cycling lane network within a 5.1 km street-network buffer around each school will be calculated using GIS (92). Additionally, school staff will be asked to provide information on the availability of bicycle racks either on school premises or near the main entrance. School engagement, which may influence the effects of the intervention, will be assessed through the perceptions of the research staff. Engagement will be categorized into three dimensions: teacher engagement (average staff perceptions of teacher involvement across all classes), student engagement (average staff perceptions of student participation across all classes), and overall school engagement (average of teacher and student engagement scores). Data for all variables will be collected during baseline and follow-up assessments and aggregated by participant and school.

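### The Phase I sample that builds the PAEE equation stops at age 16, but Phase II applies the equation up to age 17; the 4,200 m cycling rationale is also wrong as worded

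*Protocol article*

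**What the plan says.** **Age.** Section 2.2 (Study population) says that "a convenience sample of 50 students (12–16 years old) will be recruited to assess the PAEE of different modes of commuting to school". Table 2, which gives the participant criteria for Phase II, admits adolescents "aged from 12 to 17 years old (both ages included". The Introduction also takes adolescence to run from 12 to 17.

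**Use of the equation.** Section 2.7.1.2, under Primary outcomes, states: "In Phase II, PAEE related to cycling will be estimated using predictive equations developed in Phase I". Distance, speed and heart rate are given as examples of predictors. The Phase II quantity is mean VO2 and VCO2 in ml/min over each cycling trip.

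**Phase I ride.** Section 2.6.1 (Study assessment protocol) says of participants that "they will start cycling during 15-minute period along the designated route". The duration is justified by a reference distance, "we estimated a distance of 4,200 m, the threshold distance used for Australian adolescents (53", and the text continues "with which a speed of approximately 15 km/h would not exceed 15 min".

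**Phase II distance.** Table 2 sets no numeric limit on home-school distance. Intervention pupils must be able to cycle both ways at least 3 days per week, and section 2.4.1 mentions distance as one reason why some pupils will not take part.

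**The concern.** A prediction equation is supported only over the range of people and conditions in which it was developed. Here the development sample is one year of age narrower than the population in which the equation will be used, and the protocol gives no reason for the difference. The Discussion concedes that Phase I is small and may not generalise well, but it does not mention the missing age-year. The accuracy reported from Phase I would then say nothing about the oldest eligible pupils, although their predicted values enter a primary outcome.

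The protocol faults existing equations for having been derived in conditions unlike those of use, so the same test can fairly be put to its own equation.

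The rationale for the 15-minute ride also contains an arithmetic slip. It matters mainly because it blurs what distances Phase I will observe.

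**Working it through.** **1. Age ranges**

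- Phase I (section 2.2): 12, 13, 14, 15, 16, which is five age-years.
- Phase II (Table 2): 12, 13, 14, 15, 16, 17, which is six age-years.
- Not covered: age 17, so 1/6 = 16.7% of the eligible age-years.
- The protocol gives no age distribution. If ages were even, 300 × 1/6 = 50 pupils. With an assumed share of 5% to 20%, the count is 300 × 0.05 = 15 to 300 × 0.20 = 60 pupils.

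**2. The cycling sentence in section 2.6.1**

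Inputs: 4,200 m, about 15 km/h, 15 min. Formula: time = distance / speed.

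- As worded: 4.2 / 15 × 60 = 16.8 min, which exceeds 15 min by 16.8 / 15 − 1 = 12%. The plan's figure is not reproduced.
- Allowing for the approximate speed: at 16 km/h, 4.2 / 16 × 60 = 15.75 min, still too long. The statement becomes true only from 4.2 / 0.25 = 16.8 km/h.
- In the other direction: 15 km/h × 0.25 h = 3.75 km, or 3,750 m.

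For comparison, the walking half of the same rationale checks a distance against a distance: 4.4 × 0.25 = 1.10 km and 4.6 × 0.25 = 1.15 km, both below 1,350 m. That half is correct. Read in the same way, the cycling half would be correct too, since 3,750 m is below 4,200 m.

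**3. Distance as a predictor**

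- Every Phase I ride lasts 15 min, so ride distance = average speed × 0.25 h. At the level of ride means, distance and average speed carry the same information in Phase I.
- In Phase II, trip duration varies, so a trip can combine an ordinary speed with a distance that no Phase I participant rode.
- No numeric distance limit rules such trips out, and no figure in the protocol tells how many there will be.

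**The case against.** **Only a small part is affected.** Five of six age-years are covered, and nothing shows how far predictions would be wrong one year above the sampled range. Both points stand. A reader might infer that the primary outcome as a whole is extrapolated, but the documents support this only for 17-year-olds and possibly for some long trips.

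**The 4,200 m sentence is a rationale.** A reader might infer that the protocol promises to cover all trips up to 4,200 m and fails. It makes no such promise. By analogy with the walking sentence, the point was probably that a 15-minute ride stays under the threshold, which is true at 15 km/h. The wording is still wrong, because it compares with minutes.

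**A longer ride is not automatically out of range.** The outcome is a per-minute rate, and speed and heart rate are also named predictors. Section 2.6.1 prescribes no fixed cycling speed, so 3,750 m is not a ceiling on Phase I distances. This narrows the distance concern but does not remove it, because distance is named as a predictor.

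**Long trips are not shown to occur.** One might compute that 5.1 km at 15 km/h takes 5.1 / 15 × 60 = 20.4 min, 36% longer than the Phase I ride. But the 5.1 km figure is an area for measuring infrastructure: "the length of the cycling lane network within a 5.1 km street-network buffer around each school will be calculated". The PACO category for 5 km or more belongs to a questionnaire that covers every mode of travel. Neither is a cycling trip length. Schools must also be urban, and pupils must be able to cycle the route.

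**Validation might reach Phase II.** It is tempting to say that cross-validation is confined to Phase I. Section 2.7.1.2 places the Cosmed K5 measurements there, but Table 3 marks the device for energy expenditure in both phases, so the documents do not settle this.

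**Conclusion.** The age mismatch holds. The equation is developed at ages 12 to 16 and applied at ages 12 to 17, so PAEE is extrapolated for any 17-year-old enrolled. This is one of six age-years. The figure of about 17%, or 50 of 300, assumes an even spread of ages; the size of the resulting error in PAEE cannot be derived from the protocol.

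The cycling sentence is wrong as worded (16.8 min, not 15 min or less). It is a slip in a justification and changes no sample size, significance level or power.

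The distance concern holds only as a possibility: trips longer than those ridden in Phase I may lie outside the equation's range, in a number that cannot be estimated from what is given. Taken together, these are worth correcting because the age gap is avoidable and cheap to close; they do not show that the PAEE comparison between groups would be invalid.

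**What to change.** 1. In section 2.2, recruit Phase I from ages 12 to 17 within the same sample of about 50. The cost is that the sample is spread over one more year of age. This has to happen before Phase I measurement ends, because the gap cannot be closed later without new measurements.
2. In section 2.6.1, reword the cycling rationale to say either that a 15-minute ride at about 15 km/h (3,750 m) stays below 4,200 m, or that 4,200 m needs about 17 min at that speed. This costs one sentence.
3. Repeat the Phase II PAEE analysis without trips longer than those ridden in Phase I, as a sensitivity analysis, and report how many trips are removed. The GPS distances already planned serve for this, so the cost is one additional analysis.

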**Figure 1 fig1:**
[figure not shown]
School recruitment plan flow chart of the ENERGYCO study. *Expected number during the school recruitment process.

### Trial management groups

2.3

The trial management group will be composed of a steering committee of investigators responsible for overseeing all aspects of trial implementation. Their primary responsibilities include coordinating participant recruitment, ensuring compliance with study protocols, and monitoring data quality. Moreover, given the wide range of variables included in the ENERGYCO project, each investigator will be assigned a specific area of coordination: physiological variables (e.g., RMR and PAEE), physical variables (e.g., sedentary time and PA levels), psychosocial variables (e.g., self-esteem, and mental health), among others. Although the inclusion of additional oversight committees was considered, the manageable scope of this trial, combined with the expertise of the current steering committee, is considered sufficient to ensure proper trial governance and robust data quality control.

### Procedures

2.4

#### School recruitment and randomization

2.4.1

In Phase I, a convenience sample of approximately 50 students will be recruited. A call to action will be used to engage adolescents through the development of infographics and information about the aims of this phase, which will be disseminated through social media, personal contacts, or emails. Since these tests will be conducted outside the school timetable, no schools will be directly contacted. Instead, parents or legal guardians will be responsible for contacting the research team if their children are interested in participating in the study and they provide their consent. In this call to action, incentives, such as activity wristbands will be given away to participating adolescents. For Phase II, a specific selection protocol will be implemented through a random draw. A list of all public secondary schools in each of the participating cities of the government educational institutions in Andalucía will be obtained. The schools in the three cities (Granada, Almería, Jaén) will be contacted by phone, and if they are interested in participating, they will have to meet a series of inclusion and exclusion criteria presented in Table 1. During the call, a meeting will be arranged with interested schools to explain to the management team and teaching staff the main objective of the study, as well as to obtain official consent to participate in the project from the school. After that, the research staff with the help of Physical Education teachers will recruit participants and their families, by visiting selected classes and explaining the study to prospective adolescent participants and finally requesting the family’s consent. The inclusion and exclusion criteria for the participants are presented in Table 2. To complete the sample of students in the intervention group, several schools may be needed, as not all students will be able to participate in the school-based cycling intervention due to family reasons, distance, predisposition, etc. To encourage as many students as possible from the intervention school to participate (with their families’ consent) in the school-based cycling intervention, an incentive system will be planned similar to other studies (42, 43). This incentive will consist of a voucher to be redeemed for sports equipment, provided that the participant has completed the 8 weeks of intervention and presents valid data at both baseline and follow-up. Once finished the baseline assessment, the participating schools will be randomly assigned through a draw to either a control or experimental group.

**Table 1 tab1:** Schools’ inclusion and exclusion criteria.

Inclusion criteria	Exclusion criteria
The school has a specific space for parking bicycles and allows their parking	The school does not have specific infrastructure to park or store bicycles
The school has at least two classes per grade	The school offers bus transportation to the adolescents
At least eight students from the school will agree to participate in the study	The school is already participating in other interventions focused on promoting healthy behaviors
Schools from urban areas	The school has implemented an intervention to encourage commuting to school within the last year
	Schools from rural areas

**Table 2 tab2:** Participants’ inclusion and exclusion criteria.

Inclusion criteria	Exclusion criteria
Adolescents’ females and males aged from 12 to 17 years old (both ages included)	Adolescents younger than 12 years or older than 17 years
Healthy participants who can ride a bicycle safely and without difficulty.	Participants with any injury or medical condition that prevents safe participation in cycling to and from school
Be able to cycle to and from school at least 3 days per week during eight consecutive weeks (Intervention group)	Insufficient ability to ride a bicycle or inability to cycle to and from school at least 3 days a week (Intervention group)
Not to cycle to and from school more than 3 days a week during the last year	Participants who have cycled to and from school more than 3 days a week during the past year
To present a valid signed consent from their parents or legal guardians	Participants without a valid, signed parental or guardian consent form
To present valid data at baseline and follow-up from all the outcomes assessed	Participants who do not provide valid data for all assessed outcomes at baseline and follow-up

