#### Sample size calculations

2.4.2

For Phase II, at least 250 participants are needed to ensure an acceptable sample size, assuming 5% precision (*α* err prob) and a very high statistical power of 95%. (Error 1-*β* err prob) (44). This calculation has been made considering a study objective where the effect of the intervention program on the different health variables of young people is evaluated (e.g., RMR, EE, PA levels, body composition, muscle strength). In this study there will be two main comparison groups (experimental group and control group) and for this the ANCOVA statistical analysis will be performed: fixed effects, main effects, and interactions (F test) and with an effect size = 0.25. It is assumed that there will be dropouts during the school-based cycling intervention (≈15% in the experimental group), so ≈300 adolescents will be recruited from different schools in the three Spanish cities. Following the forecasts in Figure 1, 100 adolescents would be needed in each city. The groups randomization will be done at a 1:1 ratio at city level (i.e., from each city, 50 participants will be randomized to intervention and 50 to control groups), as other studies have done before (45). Nevertheless, due to the low prevalence of cycling to school in Spain (46), we will try to recruit as many schools as necessary in each city to reach the number of 100 adolescents.

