**Figure 3 fig3:**
[figure not shown]
Intervention design phase II of the ENERGYCO study.

Assessment day 1 (2): this session will include anthropometry, blood pressure, muscular strength, and motor competence assessment at an indoor sport facility.

Assessment day 2 (2 h): in this session the cardiorespiratory fitness of the participants will be assessed. Once participants have finished the test, they will have to complete an online student-questionnaire. During this session, participants will receive a belt with an accelerometer (GT3X+ accelerometers; ActiGraph, Pensacola, FL) and a Global Positioning System (GPS; QStarz BT-Q1000XT; Travel Recorder, International Co, Ltd. Taipei, Taiwan), a heart rate monitor, including chest band and watch, (Polar Ignite 10, Polar Electro Oy, Kempele, Finland) for measuring their resting heart rate during the first weekend of the baseline week, and to use it during the cycling trips to and from school.

Assessment day 3 (1 h and a half): in this session the RMR of the participants will be assessed. Participants will have to come to the indicated facility in a postabsorptive state (10–12 h without consumption of caloric food or beverages) and by passive transport. Moreover, participants from the experimental group will be provided with two links, one to fill in weekly, after the *Bikeability* sessions week, providing information about their weekly cycling experience to and from school and their opinions on the motivational strategies, and another link with access to a questionnaire to be filled in by their parents.

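### Sections 2.4.1 and 2.4.2 and Table 2 disagree on whether a school's arm is known when pupils enter; on either reading entry or retention depends on the arm, with a risk of selection bias

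*Protocol article*

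**What the plan says.** The protocol article makes the school the unit of allocation (section 2.1: "where the schools will be the units of randomization"). Section 2.4.1 gives one explicit timing rule: "Once finished the baseline assessment, the participating schools will be randomly assigned through a draw to either a control or experimental group".

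Earlier in the same paragraph, two sentences speak of arms as if they already existed. One concerns sample size in a single arm: "To complete the sample of students in the intervention group, several schools may be needed, as not all students will be able to participate". The reasons it gives include family circumstances, distance and inclination. The other introduces an incentive: "To encourage as many students as possible from the intervention school to participate". The incentive is a voucher for sports equipment, given "provided that the participant has completed the 8 weeks of intervention and presents valid data at both baseline and follow-up".

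Table 2 lists as an inclusion criterion "Be able to cycle to and from school at least 3 days per week during eight consecutive weeks (Intervention group"), with a mirror-image exclusion criterion that carries the same arm label.

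Section 2.4.2 expects 50 pupils per arm in each city and adds: "we will try to recruit as many schools as necessary in each city to reach the number of 100 adolescents". In section 2.6.1, the text on assessment day 3, the session at which resting metabolic rate is measured, says that "participants from the experimental group will be provided with two links".

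**The concern.** In a cluster trial, randomising schools protects the comparison only if the pupils who enter and are followed do not depend on the arm. Under the stated order no intervention school or intervention group exists at recruitment. A single-arm recruitment problem, a recruitment incentive for one arm and an eligibility criterion for one arm therefore have no place before the draw.

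If field staff follow these sentences and not the timing rule, pupils in one arm are chosen for living within cycling range, having family agreement and wanting to cycle, while pupils in the other arm are not. Such traits may plausibly relate to activity, fitness, body composition and hence the primary outcomes. The voucher adds a second asymmetry: it rewards valid follow-up data, but as described only in the arm that can complete the intervention.

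**Working it through.** The plan states no figure on this point, so the check is a comparison of passages, followed by an illustration of scale.

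**Step 1: the two possible orders**

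- *Arm known at recruitment.* This fits the two arm-labelled sentences in section 2.4.1, the arm-labelled criteria in Table 2 and the quota of 50 per arm per city in section 2.4.2 (whole schools of varying size will not in general split 50:50). It contradicts the post-baseline draw. Entry is then filtered by commuting feasibility in one arm only.
- *Draw after baseline.* This fits the timing rule. But the Table 2 criterion for the intervention group can then be applied only once the arm is known, by dropping pupils from that arm. Section 2.8 gives a route: the Bikeability sessions are also used to detect pupils without the capacity to carry out the intervention. Section 2.5 offers those sessions to control schools only after the eight weeks, so no equivalent check is described for controls during the trial.

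On both orders, who enters or stays depends on the arm. Table 2 does require every participant to be able to ride safely, so the asymmetry lies in feasibility of, and commitment to, commuting by bicycle and not in basic riding skill.

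**Step 2: does the analysis remove it?** Section 2.10.2 adjusts for the baseline value of the outcome and for school-level variables: area socioeconomic status, cycle lanes, bicycle parking and engagement. Individual home-school distance is measured (section 2.7.2.17) but is not named among these adjustments, and neither is willingness or family support. Section 2.10.1 makes the per-protocol set the main presentation and requires the cycling frequency of intervention pupils only, which adds further selection in the same arm.

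**Step 3: scale, under assumptions that are not in the documents.** Suppose the intervention-only criterion screens out a proportion p of pupils in that arm, and that ability or willingness to commute by bicycle is normally distributed and correlates r with the outcome. With no intervention effect, the arms then differ by

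shift = r × φ(z_p) / (1 − p), in SD units.

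With 125 per arm (250 / 2, section 2.4.2), the standard error is √(2/125) = 0.126. Type I error is for a two-sided 5% z-test, ignoring clustering and covariate adjustment.

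| p | r | shift (SD) | type I error |
|---|---|---|---|
| 0.10 | 0.1 | 0.02 | 5.3% |
| 0.10 | 0.3 | 0.06 | 7.5% |
| 0.30 | 0.2 | 0.10 | 12.3% |
| 0.50 | 0.1 | 0.08 | 9.7% |
| 0.50 | 0.3 | 0.24 | 47.3% |

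The planned effect is f = 0.25, which for two equal groups is d = 2 × 0.25 = 0.5 SD. Adjustment for the baseline outcome would remove part of the shift, but not a part that acts through change and is tied to unmeasured motivation or family support.

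**Step 4: the voucher.** It requires both completion of the intervention and valid data at both time points. A control pupil cannot meet the first condition. With 50 controls in each of three cities, 3 × 50 = 150 pupils have no described access to it.

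**The case against.** The one explicit timing rule is the safe one, and nothing says outright that a school's arm is known when its pupils are recruited. The arm-labelled sentences are forward-looking and may only describe what the future intervention arm will need. The randomisation process is also said to be in Figure 1, which is not visible in the text reviewed and may set out the order clearly.

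A reader might infer that extra schools are placed in the intervention arm, without a draw, whenever that arm is short. The documents do not support this. The Abstract says that as many schools as needed will be included and that each will be randomised, and section 2.4.2 adds schools to reach the city total of 100 across both arms. A reader might also take the links mentioned under assessment day 3 as proof that the arm is known before baseline ends. That sentence does not clearly date their issue before the draw, and the weekly link is for use after the Bikeability week. Finally, the absence of a control voucher is partly an argument from silence, and controls are offered the sessions and motivational material afterwards.

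These points limit the claim but do not dispose of it. Outright placement of schools is not shown, although the wording on completing the intervention group leaves room for it. The arm-specific criterion in Table 2 survives every reading, because it must act either at entry or after allocation. The voucher that is described is arm-specific on its own terms.

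**Conclusion.** The passages contradict each other and must be reconciled. The supported conclusion is a risk of selection bias through arm-dependent entry or removal, together with incentives to return for follow-up that differ by arm as described.

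It would go too far to say that the arms are not comparable. That allocation is known at recruitment is an inference from the arm labels, and the size of any bias cannot be computed from the documents. The range of about 0.02 to 0.24 SD, with type I error of about 5% to 47%, rests entirely on the assumed screening proportions (10% to 50%) and correlations (0.1 to 0.3), on independent observations and on no covariate adjustment. It shows only that the problem could run from negligible to about half the planned effect. The effect of the voucher on follow-up completion is likewise not quantified. The planned adjustments do not reliably remove either problem, so the correction belongs in the design.

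**What to change.** Reconcile sections 2.4.1, 2.4.2 and 2.6.1 and Table 2 around a single order:

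1. Apply the same eligibility criteria and the same consent script to pupils in all schools before the draw. Pupils should be able and willing to take part in either arm. Remove the arm label from the Table 2 criteria.
2. Complete all baseline sessions, including resting metabolic rate, and then draw schools 1:1 within each city.
3. If numbers fall short, add schools only as a further batch, drawn after its own baseline and never assigned to one arm. Delete the wording about completing the intervention group with several schools.
4. State that the experimental-group links are issued after the draw.
5. Tie the voucher to attendance at baseline and follow-up in both arms, and not to completing the cycling.

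Most of this is wording and sequence. The costs are vouchers for up to about 150 controls, arm sizes that may not be exactly 50:50 in each city, and possibly slower recruitment because pupils in future control schools must meet the same criterion.
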